### Efficacy End Points

#### Primary End Point

The primary efficacy end point is freedom from any atrial arrhythmia (defined as AF, atrial flutter, or atrial tachycardia lasting >30 seconds) off class I or III AADs through 12 months after T_0_ (completion of the intended ablation lesion set). The primary end point is evaluated from the end of a 3‐month blanking period. Recurrence may be detected on any of the following methods during scheduled or unscheduled symptom‐driven encounters and is considered met on first documentation, irrespective of frequency or symptom status.
12‐lead ECGRhythm strip7‐day Holter monitor (or any Holter >24 hours if arranged via usual clinical care)Device interrogation (where applicable)

For participants who complete the intended ablation lesion set, follow‐up timing is anchored to T_0_. Participants who undergo partial delivery of their allocated ablation strategy but are unable to complete the intended lesion set for any reason (including persistent LA thrombus precluding hybrid stage 2 or procedural complications) will remain included in the primary efficacy analysis within the prespecified modified intention‐to‐treat analysis set and end point definitions. All interstage events and procedural exposures in the hybrid arm will be prospectively captured within safety and secondary analyses. For the 12‐month binary rhythm end point, these participants will be classified on the basis of their observed rhythm status, antiarrhythmic drug use, cardioversion, and repeat ablation status, using the same end point definitions as for participants who reach T_0_. Cardioversion or repeat ablation for arrhythmia recurrence occurring after the blanking period will be considered a treatment failure for the binary rhythm end point.

Patients who demonstrate no recurrence of qualifying arrhythmia and do not require cardioversion or repeat ablation after the blanking period are considered treatment successes with respect to efficacy.

#### Secondary and Exploratory End Points

Secondary and exploratory end points will use data from investigations evaluated over the 12‐month follow‐up and are listed below:
Freedom from any atrial arrhythmia lasting >30 seconds after a single completed procedure on class I/III AADs.Freedom from atrial arrhythmias after any redo procedures (on or off class I or III AADs). This end point accounts for the overall success rate when additional ablations are performed.LV structural remodeling, as measured by change in LVEF in response to either procedure (from pre‐ to postablation echocardiography up to 12 months).LA remodeling in response to either technique (as measured from pre‐ to postablation echocardiography up to 12 months).Change in NT‐proBNP and prespecified circulating biomarkers (including CRP, lipid profile, renal function, and complete blood count) from baseline up to 12 months.To evaluate the effects of the interventions on symptoms, as assessed by change in the modified European Heart Rhythm Association score and New York Heart Association functional class from baseline up to 12 months after ablation.To evaluate the effects of the interventions on quality of life, as assessed by change (from baseline) in 3 highly validated quality‐of‐life scores:
European Quality 5 Dimensions 5‐Level scale^50^
AF Effect on Quality‐of‐Life Questionnaire^51^
Minnesota Living With Heart Failure Questionnaire^52^

#### Safety End Points

All complications occurring during the trial period will be recorded and reported. A list of expected complications is reported in Table 2, comprising adverse events and serious adverse events. The primary safety end point is defined as the incidence of major adverse cardiac events (MACEs) within 30 days of any procedure (or part of a procedure). MACEs are a widely reported composite end point in interventional and surgical cardiac trials and have been used to report outcomes in HA.^53^, ^54^ HALT AF will incorporate the 5 key components of MACEs. All procedure‐related complications will be recorded and categorized as early (within 30 days) or late (>30 days). The primary safety analysis focuses on early (30‐day) MACE rates across arms. Secondary safety outcomes are defined as the incidence of any procedural or non–procedure‐related adverse events through 12 months in each study arm.

**Table 2 jah370697-tbl-0002:** Adverse and Serious Adverse Events Expected in HALT AF

Adverse events	Serious adverse events
Bruising, hematoma, vascular injury not requiring intervention	Vascular complications requiring blood transfusion or intervention
Pericardial or pleural effusion (requiring observation only)	Symptomatic pleural or pericardial effusion requiring intervention
Pneumothorax requiring observation	Pneumothorax requiring chest drain
Chest infection or pneumonia	Empyema
Pulmonary edema	Myocardial infarction
Temporary phrenic nerve injury	Permanent phrenic nerve injury
Localized soft‐tissue infection	Stroke or transient ischemic attack
Periprocedural ventricular arrhythmia	Pulmonary vein stenosis (>70% reduction in baseline diameter)
	Procedure‐related requirement for permanent pacemaker insertion
	Cardiac trauma requiring surgical intervention
	Atrio‐esophageal fistulae
	Radiation‐induced skin injury
	Death

HALT AF indicates Hybrid Ablation for Atrial Fibrillation With Heart Failure.

#### Key MACE Composite Components Used in HALT AF

Acute myocardial infarctionStroke or transient ischemic attackCardiovascular death or any procedure‐related deathUnstable angina requiring urgent interventionHeart failure (new or worsening)

### Data and Safety Monitoring Board

The trial will be monitored independently, with annual review by an independent board that will retain oversight of the study, with additional ad hoc meetings convened as needed or if emerging safety signals or investigator concerns arise. The board will consist of at least 3 senior experts in trial methodology and trial management who are unaffiliated with the sponsor or the trial. At each review, trial progress, protocol adherence, completeness of follow‐up, and all adverse events will be discussed. In parallel, the sponsor will conduct annual monitoring of regulatory compliance, governance adherence, and completeness of safety reporting.

### End Point Adjudication

Arrhythmia end points will be adjudicated by independent clinical specialists (clinicians and physiologists) who are not involved in the delivery of the index procedure. Rhythm recordings (including ECGs, Holter monitors, and device interrogations where available) will be reviewed retrospectively and independently of the clinical encounter, with reviewers blinded to treatment allocation, procedural strategy, and clinical outcomes. In cases of disagreement or if outcomes remain undefined, consensus or a further independent clinician will be used to establish rhythm end points. Similarly, all echocardiographic analyses are to be performed by experienced readers blinded to the allocated treatment. Image acquisition will follow a standardized protocol with images anonymized at the point of acquisition and assigned coded identifiers to prevent reviewers from inferring group allocation. Measurements will be adjudicated independently by 2 observers, with discrepancies resolved by consensus or, when necessary, by a third senior reviewer. Inter‐ and intraobserver variability are to be assessed periodically in a random sample of studies.

### Statistical Analyses

The primary efficacy outcome will be analyzed using a modified intention‐to‐treat approach, including all randomized patients who undergo any component of their allocated ablation strategy. This approach was prespecified to reflect the pragmatic strategy‐based design of HALT AF, recognizing that the trial evaluates procedural strategy effectiveness and that patients without procedural exposure do not enter the risk set for procedural efficacy. Patients randomized but not exposed to any procedural component will be described separately and excluded from efficacy analyses. Participants who undergo partial delivery of the allocated strategy but are unable to complete the intended lesion set for any reason will remain in the primary efficacy analysis and will be handled in accordance with the prespecified end point rules. As a conservative sensitivity analysis, patients who are randomized but not exposed to any procedural component will be classified as treatment failures for the 12‐month binary end point.

#### Primary Efficacy Analysis

The primary end point is freedom from any documented atrial arrhythmia (AF, atrial flutter, atrial tachycardia) lasting >30 seconds between the end of the 3‐month blanking period and 12 months. The proportions of patients free from recurrent atrial arrhythmia lasting >30 seconds off AADs at 12 months after ablation, within the prespecified assessment window (T_0_+365±30 days), will be compared between treatment groups using Poisson regression with robust variance to estimate adjusted risk ratios and risk differences, with 95% CIs. The primary adjusted model will include the randomization strata (age category and sex). Poisson regression with robust variance was chosen to directly estimate risk ratios for this binary outcome. Unadjusted comparisons will be performed using the χ^2^ or Fisher's exact test, as appropriate. A time‐to‐first arrhythmia recurrence analysis will serve as the key supportive analysis. Time will be measured from T_0_ (completion of the intended lesion set) to the first documented recurrence identified on any scheduled or unscheduled rhythm monitoring after the blanking period. Participants without recurrence will be censored at the date of their most recent rhythm assessment or at the end of the prespecified follow‐up window (T_0_+365±30 days), whichever occurs first. Kaplan–Meier survival curves will be constructed, and treatment differences will be evaluated using a Cox proportional hazards model adjusted for randomization strata (age, sex). A prespecified sensitivity model will additionally adjust for baseline LVEF category (<40% and 40%–49%) and AF duration category. Time‐to‐event analyses will be performed among participants who reach T_0_. Participants who do not reach T_0_ will be summarized descriptively and included in sensitivity analyses where appropriate.

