Mechanistic insights suggest that as AF becomes persistent, the arrhythmogenic substrate extends beyond the pulmonary veins (PVs).^8^ Experimental and human studies demonstrate that increasing AF duration is associated with progressive left atrial (LA) structural remodeling, including interstitial fibrosis, myocyte hypertrophy, and chamber dilatation,^9^, ^10^, ^11^, ^12^ alongside electrophysiological changes such as conduction heterogeneity, shortening of the action potential and effective refractory period, and alterations in ion channel expression and distribution.^11^, ^13^, ^14^ High‐density endocardial and epicardial mapping studies in persistent AF have further identified extra‐PV focal sources, rotational activity, and regions of endocardial–epicardial electrical dissociation, particularly within the posterior LA, suggesting that arrhythmia perpetuation may be sustained by a 3‐dimensional substrate rather than surface triggers alone.^12^, ^15^, ^16^, ^17^

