### Study Design

HALT AF is an investigator‐initiated, multicenter, prospective, randomized controlled trial with an open‐label design and blinded evaluation of end point outcomes. Approximately 120 participants from 5 UK centers within the National Health Service will be randomized in a 1:1 ratio to convergent HA (with or without left atrial appendage [LAA] exclusion) or endocardial CA alone. Figure 1 illustrates the trial logo, and Figure 2 reports the patient pathway through the trial.

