### Patient Population

#### Inclusion Criteria

Age ≥18 yearsPersistent or long‐standing persistent AF (as defined by current guidelines)^1^
LVEF <50%*At least moderate LA dilatation (LA volume index ≥42 mL/m^2^)*Suitable for either procedure (clinical equipoise)

*As measured on transthoracic echocardiography in line with current guidelines.^35^ The LVEF threshold (<50%) is intended to capture both HF with mildly reduced ejection fraction (LVEF 40–49%) and HF with reduced ejection fraction (LVEF <40%). Baseline LVEF will be summarized both as a continuous variable and in prespecified clinically relevant categories (eg, <40% and 40%–49%).

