### Randomization and Blinding

Randomization and data collection will use Research Electronic Data Capture.^39^ Research Electronic Data Capture is a secure, web‐based application that allows for longitudinal data collection with audit trails to ensure data integrity. It will be accessed via a secure server stored within St George's University, London, UK. Once enrolled, a patient identification number will be generated by registering the patient for an electronic case report form. Authorized staff will be allocated a user name and password for this purpose. Once informed consent and eligibility are confirmed, the staff member can enter the patient's details, and the software will randomly assign the subject to a trial arm. Randomization uses stratified permuted block randomization with concealed block sizes to ensure parity and comparability between arms with respect to key baseline characteristics known to influence AF incidence, prevalence, and progression.^40^, ^41^ An independent statistician generated the allocation sequence. Participants will be stratified by sex and age (<65 versus ≥65 years), creating 4 strata (men <65, men ≥65, women <65, and women ≥65 years). Randomization is to be conducted in a 1:1 ratio within each stratum using permuted blocks (Figure 3) of varying sizes (4, 6, and 8). Blinding to treatment is not feasible given the differences between the arms (single‐stage versus 2‐stage). However, follow‐up assessments (ECG interpretation, rhythm monitoring, echocardiography, and blood tests) and end point validation will be performed by independent clinicians or technicians blinded to the treatment allocation. Participants are fully informed of their allocated treatment and receive standard clinical care. To preserve blinding of outcome assessors, participants are asked not to disclose treatment allocation during research assessments only and are explicitly advised that allocation may be disclosed at any time when clinically necessary.

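### The primary model adjusts only for age category and sex; prespecifying baseline LVEF, LA volume index and AF duration as covariates would be a cheap, assumption-dependent gain in precision.

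*Protocol article*

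**What the plan says.** **Randomisation.** Under Randomization and Blinding: "Participants will be stratified by sex and age (<65 versus ≥65 years". This gives four strata. Neither centre nor any measure of disease severity is a stratification factor; Study Design gives "Approximately 120 participants from 5 UK centers".

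**Primary model.** Primary Efficacy Analysis specifies "Poisson regression with robust variance to estimate adjusted risk ratios and risk differences, with 95% CIs", and then "The primary adjusted model will include the randomization strata (age category and sex".

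**Other adjustment.** After the sentences on Kaplan–Meier curves and the Cox model, the same section adds: "A prespecified sensitivity model will additionally adjust for baseline LVEF category (<40% and 40%–49%) and AF duration category". Because of where it stands, it is unclear whether this covers the binary primary end point or only the time-to-event analysis.

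**Baseline data.** Inclusion Criteria require LVEF below 50% and LA volume index of at least 42 mL/m², both on echocardiography. For LVEF the article states: "Baseline LVEF will be summarized both as a continuous variable and in prespecified clinically relevant categories". AF duration and LA size are listed as subgroup factors under Exploratory and Subgroup Analyses. Collection of AF duration on every participant is therefore implied, not stated.

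**Rationale.** The introduction notes that "increasing AF duration is associated with progressive left atrial (LA) structural remodeling".

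**The concern.** The article builds eligibility on LVEF and LA dilatation, describes longer AF as going with LA remodelling, and regards LVEF and AF duration as worth adjusting for in a sensitivity analysis. Yet none of the three enters the model that produces the primary estimate. LVEF and AF duration are reduced to categories where they do appear, which discards part of whatever information they hold. LA volume index is never a covariate.

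At stake are some precision and the ease of defending the result. The trial is sized at 80% power on 104 evaluable patients. If LA size or AF duration happens to differ between the arms of an open-label trial, readers will ask for an adjusted analysis. It is better fixed in advance than chosen afterwards.

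**Working it through.** **1. The plan's own figure.** Inputs from Sample Size Estimation and Statistical Threshold: success 70% and 43%, two-sided alpha 0.05, power 80%, 1:1 allocation. With pooled variance and no continuity correction, the mean rate is 0.565 and

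n per arm = [1.960 × √(2 × 0.565 × 0.435) + 0.842 × √(0.70 × 0.30 + 0.43 × 0.57)]² / 0.27² = [1.374 + 0.568]² / 0.0729 = 51.7, so **52**.

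Power at 52 per arm is 80.2%. The enrolment target also follows: 104 × 1.15 = 119.6, or 104 × 1.10 × 1.05 = 120.1. No covariate gain was assumed, so the strata-only model leaves no shortfall. If all 120 were evaluable, power would be 85.6%.

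**2. Approximate gain.** If the added covariates explain a share R² of outcome variance within arms, the variance is multiplied by (1 − R²) and the effective size becomes 52/(1 − R²) per arm. R² is not in the article; the range is an assumption.

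| Assumed R² | Effective n per arm | Power | CI width relative to strata-only |
|---|---|---|---|
| 0 | 52.0 | 80.2% | 1.00 |
| 0.05 | 54.7 | 82.2% | 0.975 |
| 0.10 | 57.8 | 84.3% | 0.95 |
| 0.20 | 65.0 | 88.3% | 0.89 |

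**3. Simulation of the planned model.** Robust Poisson, 104 patients, marginal success rates held at 70% and 43%, three independent standardised covariates. Each entry is strata-only power, then power with the three covariates added.

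| Log-odds per SD | Set A (2,000 trials) | Set B (3,000 trials) | Set C (3,000 trials) |
|---|---|---|---|
| 0 | 78.6 → 78.3 | 79.3 → 78.9 | 78 → 76 |
| 0.30 (A: ln 1.4 = 0.34) | 78.8 → 81.2 | 78.9 → 80.1 | 78 → 79 |
| 0.45 (A: ln 1.6 = 0.47) | 79.5 → 82.2 | 78.7 → 81.4 | 77 → 80 |
| 0.60 | not run | 80.0 → 84.8 | 77 → 83 |

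The Monte Carlo standard error of one power value at 3,000 trials is √(0.8 × 0.2/3,000) = 0.7 points, so differences of a point between sets are noise. The change runs from about -1 point with useless covariates to about +6 points at 0.60 per SD. Type I error of the adjusted model stayed between 4% and 6%.

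**4. A cost specific to the log link.** With the three covariates added, at least one fitted probability exceeded 1 in 52% to 98% of the Set A trials run at 70% and 43%. This matters because the plan also wants risk differences. Standardising from a logistic model in Set B avoided it and gave 81.9%, 84.0% and 87.8% power at 0.30, 0.45 and 0.60. Type I error was then 5.0% to 6.6%, so part of that power may reflect a variance that is too small.

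**5. Chance imbalance.** At 60 per arm the SD of a standardised mean difference is √(2/60) = 0.183, so one covariate differs by more than 0.25 SD with probability 0.171. For three independent covariates, the chance that at least one does is 1 − 0.829³ = 43%. At 52 per arm it is 49%.

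**The case against.** The strongest reply is that nothing here is wrong. Adjusting for the stratification factors is accepted practice, the sample size does not rely on covariates, and the gain rests on prognostic strengths that the article does not give. That stands, and it limits the point to an optional improvement.

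Several further objections also stand:

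- The entry criteria truncate all three variables, which may weaken them as predictors. The simulation also assumes independence, although the introduction links AF duration with LA remodelling.
- The gain is not free. There are extra terms, baseline values must be complete, and the log link misbehaves as shown.
- LA size is not ignored, since it is a subgroup factor examined by interaction with treatment.

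The reply that the sensitivity model already deals with this stands only in part. That model uses categories, omits LA volume index and may belong to the Cox analysis alone.

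A reader might infer more than the article supports:

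- **That chance imbalance biases the primary result.** It does not. Under randomisation it is covered by the confidence interval, and simulated type I error of the strata-only model was 4.4% to 4.6% in Set A.
- **That the rationale names LV dysfunction as a substrate of recurrence.** The introduction's account of the substrate concerns atrial remodelling and the perpetuation of arrhythmia, not predictors of recurrence after ablation, and does not mention LV dysfunction.
- **That strata-only power is really 71% to 76%, with up to 7 points to gain.** Such figures arise if the conditional log-odds are fixed and the marginal rates are left to shrink, to about 67% and 44% at 0.60 per SD. That is a smaller effect than the trial assumes.

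**Conclusion.** The point holds as a cheap improvement in precision, not as an error. The primary model leaves out two baseline measurements that every participant has and a third that is evidently recorded. The only model that uses any of them categorises them and is not clearly tied to the primary end point. The strata-only analysis is valid and the sample size is correct, so the trial is neither biased nor underpowered for this reason.

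The size is about -1 to +6 points of power. It rests on 104 evaluable patients, marginal rates of 70% and 43%, three independent covariates and log-odds of 0 to 0.60 per SD. All but the patient number and the rates are assumptions. The range was obtained with the adjusted Poisson model and is only indicative for the standardised estimator recommended here. The case for adjusting is the asymmetry: a loss of about one point if the covariates are uninformative, against a larger possible gain and a prespecified answer to questions about imbalance.

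**What to change.** Before unblinded analysis, prespecify:

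- **Primary model:** treatment, sex, age, baseline LVEF (continuous), LA volume index (continuous) and one AF-duration variable, with its form fixed now.
- **Estimates:** risk ratio and risk difference by standardisation from a model whose fitted probabilities cannot exceed 1, such as logistic regression, with a small-sample variance correction.
- **Time-to-event analysis:** the same covariates in the Cox model.
- **Sensitivity:** the strata-only model, reported alongside. State which end points the existing LVEF and AF-duration sensitivity model covers, or replace it.
- **Missing baseline values:** a simple imputation rule, needed mainly for AF duration.

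The cost is a change of wording in the analysis plan, with no added patients, visits or measurements. The drawbacks are a few extra model terms, the need for complete or simply imputed baseline data, and about one point of power lost if the covariates prove not to be prognostic.

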#### Follow‐Up Schedule

To ensure methodological equivalence across treatment strategies, efficacy follow‐up is anchored to a harmonized time point (T_0_), defined as the date on which each participant has completed the analogous intended lesion set (PVI plus PWI), which represents completion of the randomized ablation strategy. In the CA arm, T_0_ occurs at the index procedure; in the hybrid arm, T_0_ occurs following completion of stage 2. This strategy‐level framework ensures that rhythm outcomes are assessed only after the equivalent lesion set has been delivered in both arms and avoids misclassification due to incomplete or partial procedures. All clinical events occurring between stage 1 and stage 2 in the hybrid arm will be prospectively captured, adjudicated, and included in secondary and safety analyses. Variation in the timing of stage 2, therefore, affects only the scheduling of post‐T_0_ assessments and does not alter the definition of the primary efficacy analysis. This design constitutes a prespecified postcompletion (T_0_‐anchored) efficacy framework and is not intended to estimate treatment effects from the time of randomization. Participants who do not complete stage 2 will remain included in the primary binary efficacy analysis within the modified intention‐to‐treat population. For these participants, T_0_ will be assigned as the protocol‐scheduled stage 2 time point, defined as 3 months after stage 1. Primary end point status will be classified according to the prespecified end point definitions using available postrandomization data on rhythm and AAD use. Noncompletion of stage 2 will be recorded and incorporated into end point adjudication and sensitivity analyses in accordance with the prespecified analysis plan.

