#### Statistical Threshold

All tests will be 2‐sided, with a *P* value <0.05 considered statistically significant. Estimates will be interpreted in the context of effect sizes and CIs. Analyses will be performed using R version ≥4.3 (R Foundation for Statistical Computing, Vienna, Austria), SAS version 9.4 (SAS Institute, Cary, NC), or equivalent validated analytical platforms. No formal interim efficacy analyses are planned.

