### Sample Size Estimation

The sample size was calculated on the basis of expected differences in arrhythmia‐free survival between the 2 treatment arms. Estimates will be interpreted in the context of CIs and effect size rather than significance alone. Prior data from a pilot study^55^ and published trials and analyses^5^, ^30^ were used to estimate procedural success rates, which were interpreted conservatively given the high‐risk nature of the study population. The sample size is based on a 1:1 randomized allocation to test the superiority of HA over CA. The power calculation assumed an anticipated incidence of sinus rhythm of 70% in the hybrid arm and 43% in the catheter arm. Using these numbers, with a standard α level of 0.05 and 80% power, 52 patients per arm (104 total) would be required to demonstrate the superiority of HA over CA. To account for potential dropout, loss to follow‐up, and estimation uncertainty, a 10% attrition rate and an additional 5% safety margin were applied. The final enrollment sample size was set at a minimum of 120 patients (60 per arm). The trial is powered for the primary efficacy end point; secondary and subgroup analyses are supportive and exploratory.

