## Limitations

HALT AF is a pragmatic strategy trial evaluating outcomes following randomization to catheter or hybrid ablation, with efficacy analyses reflecting treatment allocation rather than procedural optimization, and follow‐up aligned with real‐world clinical pathways. The trial, therefore, assesses the consequences of selecting a hybrid versus catheter ablation strategy rather than attempting to harmonize inherently different procedures. Within this framework, the hybrid approach entails a greater up‐front procedural burden than single‐stage endocardial‐only CA and requires completion of both epicardial and endocardial components to achieve the intended electrophysiological end points (PVI and PWI). Differences in procedural burden, recovery, and cumulative exposure are intrinsic to the strategies being compared and are explicitly accounted for in the trial design and reporting framework. Interstage events are prospectively captured and incorporated into prespecified safety and secondary analyses. Participants who do not complete stage 2 remain included in the primary efficacy analysis according to prespecified end point definitions, with additional per‐protocol and sensitivity analyses assessing robustness.

Additional heterogeneity arises from the discretionary exclusion of LAA in the HA arm for thromboembolic risk management. LAA exclusion is neither protocol‐mandated nor randomized and is not intended as a rhythm‐control intervention. The effect of mechanical epicardial LAA exclusion on AF recurrence remains uncertain, and randomized studies evaluating comparable mechanical epicardial LAA exclusion strategies have not demonstrated consistent reductions in AF burden beyond conventional ablation.^72^ To ensure transparency, all LAA interventions will be prospectively recorded and reported. Rhythm outcomes will be presented descriptively by LAA‐exclusion status, with prespecified sensitivity analyses examining the consistency of strategy‐level findings; these analyses are exploratory. End point adjudication is blinded to procedural details, ensuring that LAA management does not influence event classification.

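### The key supportive time-to-event analysis drops hybrid patients who do not complete stage 2, although the plan already assigns them a T0 and keeps them in the primary binary analysis

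*Protocol article*

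**What the plan says.** All references are to the protocol article.

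- **Primary Efficacy Analysis.** Time to first recurrence is named as the key supportive analysis of the primary end point. Time runs from T0, and time-to-event "analyses will be performed among participants who reach T_0". Everyone else is described, and enters sensitivity analyses only where that is judged appropriate.
- **Follow-Up Schedule.** T0 is the date on which the intended lesion set (PVI plus PWI) is complete: the index procedure in the catheter arm, and completion of stage 2 in the hybrid arm. Participants who do not complete stage 2 stay in the primary binary analysis, with T0 set at the scheduled "stage 2 time point, defined as 3 months after stage 1".
- **Primary End Point.** Persistent left atrial thrombus before stage 2 and procedural complications are given as examples of why a lesion set may not be completed.
- **Statistical Analyses.** The modified intention-to-treat (mITT) set is defined as "including all randomized patients who undergo any component of their allocated ablation strategy". The exclusion sentence, and the sensitivity analysis that counts excluded patients as failures, name only patients who had no procedure at all.
- **Limitations.** The trial is described as a strategy trial, "with efficacy analyses reflecting treatment allocation".

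**The concern.** Two analyses of the same end point use different patients, and what separates them is an event after randomisation. By design that event arises almost only in one arm. A catheter patient needs one procedure to reach T0. A hybrid patient needs a second admission, planned about 8 to 16 weeks after the first.

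The patients left out are unlikely to be a random sample of the hybrid arm. The examples given are thrombus and complications, and the Treatments section says that isolation may not be complete without stage 2. Leaving them out probably raises hybrid freedom from arrhythmia in the Kaplan-Meier curves and the Cox model.

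The exclusion is also unnecessary, because the plan has already given these patients a time origin. At stake is whether the key supportive analysis can corroborate the primary result. It could look stronger than the binary analysis, or appear to disagree with it, only because the patient sets differ.

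**Working it through.** **1. The plan's own figure.** Inputs from Sample Size Estimation: "anticipated incidence of sinus rhythm of 70% in the hybrid arm and 43% in the catheter arm", and "with a standard α level of 0.05 and 80% power, 52 patients per arm (104 total) would be required". Statistical Threshold makes tests two-sided. With pooled variance, p̄ = (0.70 + 0.43)/2 = 0.565:

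n = [1.960 × √(2 × 0.565 × 0.435) + 0.842 × √(0.70 × 0.30 + 0.43 × 0.57)]² / 0.27² = (1.374 + 0.568)² / 0.0729 ≈ 51.7, so 52 per arm.

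The stated figure reproduces. By the same method, power at 60 per arm is 85.6%. The sample size is not in dispute; 70% and 43% serve below as working rates.

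**2. Effect of dropping non-completers.** The documents give no non-completion rate and no success rate for non-completers, so both are assumptions. Let f be the share of the hybrid arm that does not complete stage 2 and q their success rate, with completers at 70%.

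- Hybrid freedom with everyone kept = (1 − f) × 0.70 + f × q
- Hazard ratio under proportional hazards = ln(hybrid freedom) / ln(0.43)
- Completers only: ln(0.70)/ln(0.43) = 0.357/0.844 = 0.42, whatever f and q are

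| f (of 60) | q = 0 (all recur) | q = 43% | q = 70% |
|---|---|---|---|
| 5% (3) | 66.5%, HR 0.48 | 68.65%, HR 0.45 | 70%, HR 0.42 |
| 10% (6) | 63.0%, HR 0.55 | 67.3%, HR 0.47 | 70%, HR 0.42 |
| 20% (12) | 56.0%, HR 0.69 | 64.6%, HR 0.52 | 70%, HR 0.42 |

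The planned analysis would show 0.42 in every cell. In the last column that is correct and there is no bias.

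**3. No true difference between strategies.** Suppose freedom is 43% overall in both arms and all hybrid non-completers recur. Completers then show 0.43/(1 − f): 45.3%, 47.8% and 53.75% for f = 5%, 10% and 20%. The hazard ratio is 0.94, 0.88 and 0.74 instead of 1.

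**4. The mITT wording, side by side.** Inclusion requires a component of the *allocated* strategy. The explicit exclusion, and the analysis counting excluded patients as failures, cover only patients with *no* procedural component. A patient who receives only the other arm's procedure may fail the first rule without falling under the second. For scale, suppose 10% of the hybrid arm had catheter ablation only, with 43% success. Kept as randomised, the hybrid rate is 0.90 × 0.70 + 0.10 × 0.43 = 67.3%. The difference is then 24.3 points instead of 27.0, and power at 60 per arm is 77.0% instead of 85.6%.

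**The case against.** The strongest reply is that the primary result is untouched. Follow-Up Schedule, Primary End Point, Statistical Analyses and Limitations all keep partially treated patients in the binary analysis, and the trial is powered for that end point. This stands: a reader might infer that the primary comparison is biased by the T0 restriction, and the text does not support that.

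Second, the restriction is declared. The plan says that it does not estimate effects from randomisation, it mentions sensitivity analyses, and it refers the handling of missed stage 2 procedures to an analysis plan that is not shown. This stands in part. Anchoring time at T0 is a legitimate choice, but it does not explain why the binary and time-to-event analyses use different patients. A sensitivity analysis run where appropriate does not undo a stated rule for the main one.

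Third, a reader might infer that only hybrid patients are removed. That goes too far. If T0 strictly requires achieved isolation, a catheter patient in whom isolation was judged impossible also never reaches it, which would work against the suggested direction. If T0 is simply the procedure date, this issue falls away. The plan supports both readings, so bias towards hybrid is likely but not certain.

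Fourth, a reader might infer that the mITT set definitely drops patients treated off their allocation, mainly from the hybrid arm. The wording is ambiguous: stage 2 is itself endocardial ablation, so a hybrid patient who has only that could count as having had a component. The rule reads the same for both arms and no off-allocation rates are given, so no imbalance is shown.

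**Conclusion.** The inconsistency is real: one section gives stage 2 non-completers a T0, and another leaves them out of the key supportive analysis for not reaching it. The exclusion falls almost entirely on the hybrid arm and probably favours it. It affects the supportive analysis only.

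The size depends on unstated rates. At 10% non-completion, the hazard ratio shown is 0.42 where the full set would give between 0.42 (non-completers do as well as completers) and 0.55 (all recur), with 0.47 if they do as well as catheter patients. These figures assume the planning rates and proportional hazards, and ignore censoring.

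The mITT point is one of unclear wording. It calls for clarification and one added sensitivity analysis. It does not show that the prespecified primary set must be replaced, which would be a design trade-off.

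**What to change.** 1. Run Kaplan-Meier and Cox on the same mITT set as the binary end point, using the T0 already assigned (three months after stage 1) for patients who do not complete stage 2.
2. For these analyses, take T0 as the end of the index catheter procedure or of stage 2, whether or not isolation was achieved.
3. Keep the analysis of participants who reach T0 as a named sensitivity analysis.
4. State whether patients who receive only the other arm's procedure belong to the mITT set. Add a sensitivity analysis of all randomised patients as allocated, using observed rhythm status for those treated off their allocation.

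The cost is revised wording and a little more analysis work, with no new visits or tests. The supportive estimate may be less favourable to hybrid. The changes should be settled before outcomes are unblinded for analysis.
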